## Abstract

**Background:**

Patients undergoing emergency surgery for peritonitis are at increased risk of abdominal wall-related complications. In patients with peritonitis, the risk of incisional hernia (IH) is extremely elevated. The evaluation of quality of life of patients with incisional hernia showed lower mean scores on physical components of health-related quality of life and body image. Furthermore, the arise of a post-operative abdominal wall complication (i.e., wound dehiscence, evisceration and IH) greatly increases morbidity and mortality rates and prolongs the hospitalization.

**Methods:**

The present study aims to evaluate the efficacy of the use of a swine dermal collagen prosthesis implanted preperitoneally as a prophylactic procedure in urgency/emergency setting against abdominal wall complications in patients operated with contaminated/infected field in peritonitis. The sample size was defined in 90 patients divided in two arms (prosthesis positioning versus normal wall abdominal closure). The follow-up will be performed at 3, 6, and 12 months after surgery. The percentage of incisional hernias, wound infections, and adverse events will be investigated by physical examination and ultrasound.

**Discussion:**

The objective is to evaluate the possibility to reduce the incisional hernia rate in patients undergoing urgent/emergent laparotomy in contaminated/infected field with peritonitis by using swine dermal collagen prosthesis preperitoneal positioning as a prophylactic procedure.

**Trial registration:**

ClinicalTrials.gov NCT04681326. Registered (retrospectively after first patient recruited) on 23 December 2020.

## Introduction

### Background and rationale

Patients undergoing emergency surgery for peritonitis are at increased risk of abdominal wall-related complications. In patients with peritonitis, the risk of incisional hernia (IH) is extremely elevated. The incidence of IH in patients operated with peritonitis is up to 54%, compared with an incidence of 11–26% in the general surgical population [1–3]. Moreover, up to 24.1% of patients with peritonitis undergoing emergency laparotomy may develop fascial dehiscence [4]. The evaluation of quality of life of patients with IH showed lower mean scores on physical components of health-related quality of life and body image [5]. The prophylactic mesh implantation demonstrated to reduce the incisional hernia rate in patients undergoing vascular or bariatric procedures [6–8]. However, the intraperitoneal non absorbable mesh implantation in infected fields is generally considered at least of doubtful safety because of the theoretical increased risk of chronic mesh infection and enterocutaneous fistula [9–11]. Most incisional hernias develop during the first 3 months after surgery, which represents the critical period for the healing of transected muscular and fibrous layers of the abdominal wall [12]. However, most studies recommended a long-term follow-up period of up to at least 5 years for midline abdominal incisions to determine the real incisional hernia rate [13, 14]. The midline abdominal incision is preferred in abdominal surgery, as it provides wide and rapid access compared other incisions. However, the incidence of incisional hernias is higher following midline abdominal incisions than in other abdominal incisions [15]. In emergency surgery, the midline incision in the majority of cases is a necessity. Several factors affect the process of wound healing: surgical site infection, poor surgical technique, and patient-related factors (i.e., peritonitis, old age, obesity, diabetes mellitus, nutritional deficiencies, hepatic cirrhosis, jaundice, renal impairment, malignancy, cardiac disease, chest problems, previous abdominal incisions, steroid therapy). Data about the use of biological prosthesis in infected fields are scarce and derive principally from case reports and case series [16]. However, indications about their use and usefulness in infected fields have been recently published by the Italian Biological Prosthesis Working Group (IBPWG) [16]. A previously published prospective observational study evaluated the efficacy of implantation of biological prosthesis in high risk patients in order to reduce the incidence of incisional hernia. This study suggested the efficacy of this kind of prosthesis in reducing incisional hernia rate in patients with multiple risk factors [17]. A recently published meta-analysis showed as the use of biological prosthesis in ventral hernia repair resulted in a lower infectious wound complication rate but in an similar recurrence rate. These results support the application of biological prosthesis in high risk patients [18]. One recent systematic review evaluated the positive effect on incisional hernia rate of the prophylactic mesh positioning in high risk patients [19]. No randomized trials have been published since now about the use of biological prosthesis in contaminated or infected fields. The primary endpoint is to evaluate the incisional hernia rate after laparotomy at 3–6–12 months in patients with or without the mesh. So, the rationale of the trial is to evaluate the efficacy of the use of swine dermal collagen prosthesis implanted preperitoneally as a prophylactic procedure against incisional hernia in patients operated in urgency/emergency setting in contaminated/infected fields with peritonitis. The aim of the study is to reduce the incidence of incisional hernia from 50% to 20%.

### Basic information

Swine dermal collagen prosthesis is an acellular collagenic membrane of swine origin deatigenated and naturally cross-linked. The prosthesis is latex free and free from phthalates. This system allows to eliminate the antigenic cellular component maintaining the extracellular collagenic components. These factors enhance the host tissue cells ingrowth into the prosthesis. Production and shipment of the prosthesis are performed according to the international standards EN ISO 13485:2016 and EN ISO 13485:2016.

## Methods/design

### Objective

The primary objective is:

1) Evaluate the possibility to reduce the incisional hernia rate (from 50% to 20%) in patients undergoing urgent/emergent laparotomy in contaminated/infected field with peritonitis by using swine dermal collagen prosthesis preperitoneal positioning as a prophylactic procedure.

The secondary objective is:

1) Evaluate the impact on morbidity and mortality of the systematic swine dermal collagen prosthesis preperitoneal positioning as a prophylaxis for incisional hernia in patients operated in contaminated/infected field with peritonitis.

### Ethics

The trial will be conducted in accordance with the Declaration of Helsinki and according to local and regional ethical standards. The study was approved by the Local Ethical Committee on 06 February 2020 with protocol number 506/2019/DISP/AOUPR.

### Study endpoint

The primary endpoint is to evaluate the incisional hernia rate at 3, 6, and 12 months after surgery in each group (study arm and control arm). The secondaries endpoints are to define morbidity (adverse events (AE) and serious adverse events (SAE)), surgery time, time to drain removal, length of stay in hospital, and mortality.

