### Assessments for efficacy

At discharge (visit 3), and at follow-up evaluations (visits 4, 5, and 6), the patient will be evaluated for post-surgical complications (such as hematoma/seroma, wound infection, reinterventions). Complications will be evaluated by the surgeon during surgery and at discharge. Any complications will be recorded in the CRF. If the complication leads to additional surgical interventions, it needs to be noted in the CRF. The need for blood transfusions will be noted in the CRF.

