### Statistical analysis

Only the data of participants who complete the follow-up will be considered. Descriptive analysis will be performed for all pre-operative, operative, and follow-up information. For categorical variables, we will use chi-square test, for non-categorical one the *t*-test. The primary endpoint, % of patients presenting incisional hernia at 3, 6, and 12 months, will be analyzed between treatment groups using a logistic regression model, presenting odds ratio comparisons of the two. Surgery time, time to drain removal and length of stay in hospital will be analyzed between treatment groups using Student’s *T* test if data are normally distributed and with Mann-Whitney test if data are not normally distributed. The distribution of data will be evaluated with the Shapiro-Francia test. The number of patients who died will be analyzed between treatment groups using a chi-square test.

All statistical comparisons will be based on two sided tests with a 5% significance level.

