## Discussion

To date, no randomized clinical trials have examined the efficacy of biological mesh in contaminated field, and no previous data exist on the efficacy of swine dermal collagen prosthesis in preventing incisional hernia in peritonitis patients.

Our randomized controlled trials have the aim to evaluate the impact of biological prosthesis in contaminated field, reduce the incidence of incisional hernia from 20 to 50%, and determine the impact on morbidity and mortality of the systematic swine dermal collagen prosthesis preperitoneal positioning.

The result of our study will increase the knowledge about swine dermal collagen prosthesis in peritonitis patients. The long follow-up of over 36 months would permit to understand the rate of incisional hernia in the medium-long term by comparing the patients treated with the biological prosthesis and those on which traditional treatment was performed. If the use of the swine biological prosthesis will prove to be an advantage (or disadvantage) in terms of reducing early and late post-operative complications (wound infections, seroma, wound dehiscence, bleeding, incisional hernia, re-surgery), it will probably be possible to draw up more precise guidelines in case of median laparotomies during surgery for peritonitis. In fact, the absence of clear indications on the approach in case of laparotomies on infected fields leads the surgeon to have random and different behaviors from case to case without determine the cause of possible post-operative complications.

Moreover, surgery performed in urgency for peritonitis is accompanied by a percentage of complications that are certainly higher than elective surgery. Trying to understand if it is possible to reduce the percentage of complications due to incisional hernias could also help to reduce the direct and indirect costs associated with surgery. Thus, studies that are aimed to determinate if it is possible are needed. The results of this trial will support a tangible decision-making process for choosing appropriate technical approach in abdominal parietal synthesis in peritonitis.

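### The endpoint list defines morbidity only as AEs and SAEs, although the protocol elsewhere treats wound infection and other wall complications as outcomes in their own right; for these and for deaths it plans only chi-square tests

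*Protocol article*

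**What the plan says.** Four places in the protocol article describe what will be learned about complications, and they do not agree.

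- **Study endpoint.** The section states "The secondaries endpoints are to define morbidity (adverse events (AE) and serious adverse events (SAE". The other secondary endpoints are the duration of surgery, when drains come out, hospital stay and death. No wound or wall complication is listed; incisional hernia is the primary endpoint.
- **Abstract, Methods.** "The percentage of incisional hernias, wound infections, and adverse events will be investigated by physical examination and ultrasound". Wound infection stands beside adverse events as an outcome of its own.
- **Assessments for efficacy.** At discharge and at the 3-, 6- and 12-month visits, "the patient will be evaluated for post-surgical complications (such as hematoma/seroma, wound infection, reinterventions"). The section also provides for documentation: "Any complications will be recorded in the CRF".
- **Discussion.** Better guidelines are to follow if the prosthesis proves to be an advantage or disadvantage in "reducing early and late post-operative complications (wound infections, seroma, wound dehiscence, bleeding, incisional hernia, re-surgery").

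The Statistical analysis section has no sentence specific to AEs, SAEs or morbidity. It promises descriptive analysis of all pre-operative, operative and follow-up information, a general chi-square test for categorical variables, and for mortality: "The number of patients who died will be analyzed between treatment groups using a chi-square test". An effect measure, the odds ratio, is named only for the primary endpoint. The section opens by restricting the data to participants who complete follow-up.

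**The concern.** The secondary objective is the impact of the prosthesis on morbidity and mortality. For an implant placed in a contaminated or infected field, the natural safety question is whether the wound and abdominal wall do worse. The Introduction raises that kind of concern itself, for non-absorbable mesh placed intraperitoneally, when it cites chronic mesh infection and fistula. Yet the section that fixes the endpoints offers only AEs and SAEs.

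Two things are at stake. First, complications that are recorded but not named as endpoints can be selected, grouped or left out once results are known. Follow-up assessors are unblinded, which makes this more than a formality. Second, AEs after emergency surgery for peritonitis will include many events that a closure technique cannot influence. A broad AE summary would then show little of a harm confined to the wound. With only a p-value for the complications and for deaths, a reader could not tell a small difference from an imprecise one.

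**Working it through.** **The plan's own figure.** Sample size gives 45 per arm (90 in total). The aim is hernia 50% v 20%, tested two-sided at 5%. Power is not stated; 80% is assumed here. The two-proportion formula with continuity correction returns 45 per arm, an exact match; without the correction it returns 39. The trial is therefore sized for a 30-point difference in hernia, not for complications or deaths.

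**Is a wall complication an outcome?**

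| Complication | Abstract | Assessments for efficacy | Discussion | Study endpoint |
|---|---|---|---|---|
| Wound infection | yes | yes | yes | no |
| Seroma | no | yes (with haematoma) | yes | no |
| Reintervention / re-surgery | no | yes | yes | no |
| Dehiscence, bleeding | no | not named; any complication is recorded | yes | no |

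The mismatch is visible without any calculation.

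**What pooling would do, if it were done.** The article gives no complication or AE rates, so all rates here are assumptions. Let *w* be the wall-complication rate and *q* the rate of other AEs, taken as equal in both arms and independent of wall complications. Then

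any-AE rate = 1 − (1 − q)(1 − w).

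For w = 20% v 40%:

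- q = 50%: 1 − 0.5 × 0.8 = 60% v 1 − 0.5 × 0.6 = 70%. The 20-point excess becomes 10 points.
- q = 90%: 1 − 0.1 × 0.8 = 92% v 1 − 0.1 × 0.6 = 94%. It becomes 2 points.

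Power is the exact binomial power of the Pearson chi-square test, two-sided 5%, 45 per arm:

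| Assumed wall rates | Compared directly | Pooled, q = 50% | Pooled, q = 90% |
|---|---|---|---|
| 20% v 40% | 56% | 17% | 8% |
| 30% v 45% | 31% | 12.5% | 6.7% |

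**Deaths.** By the same method, power is 28% for 10% v 20% and 42% for 15% v 30%. A log-rank test hardly helps. With approximate formulas for both tests, 10% v 20% gives 26% for chi-square and 28% for log-rank; 10% v 30% gives 67% and 74%. The limit is the 45 per arm, not the choice of test.

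**Precision of a risk difference.** Wald half-width = 1.96 × √[(p₁(1 − p₁) + p₂(1 − p₂))/45].

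- 10% v 20%: 1.96 × √[(0.09 + 0.16)/45] = 14.6 points
- 15% v 30%: 1.96 × √[(0.1275 + 0.21)/45] = 17.0 points
- 20% v 40%: 1.96 × √[(0.16 + 0.24)/45] = 18.5 points
- 30% v 45%: 1.96 × √[(0.21 + 0.2475)/45] = 19.8 points

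**The analysis set.** A patient who dies before the 12-month visit cannot complete follow-up. Read literally, the completers-only rule removes that patient from the mortality comparison that is meant to count the death.

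**The case against.** The strongest reply is that nothing is lost. Wound infection, haematoma/seroma and reinterventions are assessed at discharge and at every follow-up visit, and any complication goes into the CRF. As yes/no variables they fall under the promised descriptive analysis and the general chi-square test, so the direct comparison is already available. Hernia, one of the Discussion's complications, is the primary endpoint. Grouping of AEs, intervals and sparse-count rules are commonly left to a full protocol or SAP. All of this stands, and it limits the point. It does not remove the inconsistency: a general rule for every categorical variable gives wound infection no standing as an endpoint, while the Abstract and Discussion treat it as one.

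A reader might go further and infer that morbidity will be analysed as one any-AE count, so that a harm would necessarily look like no difference. The article does not support this. It names AEs and SAEs without saying how they are summarised, and tabulation by type fits the wording equally well. Even pooled, a 20% v 50% difference in wound infection keeps power of roughly 0.19 to 0.52 when other AEs occur in 70% to 30% of patients. Nor does the article swell the AE count with all abnormal laboratory values: the phrase in Follow-up of adverse events concerns medical care and is limited to values related to the trial.

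A reader might also conclude that the chi-square test is wrong for deaths. Over a fixed follow-up it is acceptable. Replacing it with an exact test would generally make harm harder to flag: 4 v 0 events of 45 gives p = 0.041 by Pearson and 0.117 by Fisher.

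**Conclusion.** The point holds as a mismatch between the endpoint list and the rest of the article, together with an analysis of complications and deaths that plans tests without effect sizes, in completers only. The mismatch rests on the text alone.

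The dilution is conditional. It would arise only if morbidity were summarised as any AE, and its size (power of 56% falling to between 17% and 8% for 20% v 40%) depends on assumed wall rates, assumed other-AE rates of 50% to 90%, and independence between the two. Low power for complications and deaths comes from a sample sized for hernia and would remain under any test. That is the reason to report estimates with intervals and to say plainly that a non-significant result does not show safety. It is worth correcting: the secondary objective depends on it and the complications are already being recorded.

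**What to change.** **Study endpoint.** Add a secondary endpoint: abdominal-wall and surgical-site complications to 12 months, as the proportion of patients with any of wound infection, seroma/haematoma, dehiscence, bleeding, prosthesis infection or wall re-operation, and each component separately. Keep the AE and SAE tables as descriptive.

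**Statistical analysis.** For this endpoint, its components and deaths, report risk differences with 95% confidence intervals (Newcombe or Miettinen-Nurminen). The chi-square test can stay. Analyse them in all randomised patients rather than only those who complete follow-up, so that deaths before 12 months are counted. State that a non-significant difference is not evidence of safety.

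**Cost.** Wording in two sections; the existing visits and CRF already record complications. The article reports six patients enrolled; if the change is made at about that stage, it is still largely a pre-specification. The downside is that intervals of about ±15 to 20 points will show how little 45 per arm can say about harm.

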### Study design

This is a prospective, randomized controlled, post-marketing clinical study with medical device. The trial is proposed as multicentric with coordinator University Hospital of Parma (Emergency and Acute Care Surgery, Parma University Hospital, Parma, Italy). Now, there is only one other center that enlist patients that is University Hospital of Pisa (Emergency Surgery Unit, Pisa University Hospital, Pisa, Italy). There exists the possibility that other centers, once seen the published protocol, will ask to join the study. The eventuality will be evaluated and discussed. The number of subject to be enlisted is 90, 45 for each group (study arm and control arm). At the moment, the number of patients that are enlisted is only six. The few numbers of patients is correlate with the reduction of access in ED during COVID-19 pandemic and for the increased number of patients that is treated with open abdomen (that is an exclusion criteria for the study). In reality, the number of screened patients for the study is higher, but many are not eligible because they do not meet the eligibility criteria and others refuse to participate at the study.

### Trial schedule

Figure 1 is the time-lapse of the trial, from the approval by the Local Ethics Committee to the end of the study.

**Fig. 1 Fig1:**
[figure not shown]
Trial time-lapse

### Eligibility criteria

The inclusion criteria are:
Patients aged ≥ 18 years oldClinical and/or laboratory and/or radiological evidence/signs of peritonitis of any origin (peritoneal reactivity, positive Blumberg sign, fever, free air/fluid in abdominal cavity, leukocytosis, increased PCR, lactic dehydrogenase (LDH), tachycardia, tachypnea, clinical or radiological evidence/suspect of bowel ischemia)Eventual strong suspect of possible bacterial translocation (reduction of the natural intestinal barrier against bacterial translocation, i.e., bowel ischemia, bowel overdistension, intestinal occlusion, etc.)Surgical indication for midline laparotomy independently from eventual previous laparotomies

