**Fig. 2 Fig2:**
[figure not shown]
Graphical flow chart

The randomization is due electronically by an online software (https://prophybiom.easycrf.cloud). The sequence of allocation has been generated by a statistician who is independent by the study. The randomization is simple and the allocation is 1:1 to each arm. The allocation sequence is accessed only when it is requested. The randomization is due electronically by the online software when the surgeon inserts the patient in the online form.

The patient is associated at an alphanumerical code that is constituted by three parts:
First, two letters indicate the center of intervention (for example PR for University Hospital of Parma, PI for University Hospital of Pisa);Second, two numbers indicate the chronological sequential number of allocation (for example 01, 02, 03, etc.);Last, letter indicates the control group (A) or trial group (B).

So, for example, a patient that has positioning of the mesh at the University Hospital of Parma could have an alphanumerical code like “PR05B.”

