### Visit procedures

The randomization and the study data are collected using an online form (https://prophybiom.easycrf.cloud). The access at this form is allowed only at the participant at the study that has a username and password. Investigators who conduct follow-up assessments will not be blinded.

The study comprises of the following visits (Table 1):

**Table 1 Tab1:** Time and event chart

Nomenclature	Visit 1	Visit 2	Visit 3	Visits 4, 5, and 6
	Screening	Treatment	Discharge	Follow-up
	Screening, baseline	Surgery	Discharge	Follow-up
**Informed consent**	**√**			
**Inclusion/exclusion criteria**	**√**			
**Demographic data (sex, age, weight, height, BMI)**	**√**			
**Medical history/concomitant illness**	**√**			
**Physical examination**	**√**		**√**	**√**
**ASA classification**	**√**			
**Vital signs**	**√**	**√**		
**Body weight and height**	**√**			
**ECG (12 lead)**	**√**			
**Hematology and coagulation parameters**	**√**		**√**	
**Blood chemistry**	**√**		**√**	
**Antibiotic therapy**	**√**			
**Start of LMW heparin**	**√**			
**Concomitant medication**^**a**^	**√ continuously**			
**Start and end of surgery**		**√**		
**Site and length of incision**		**√**		
**Peritonitis grade assessment**		**√**		
**Peritoneal fluid sampling for microbiological examination**		**√**		
**Contamination assessment**		**√**		
**Intestinal resection**		**√**		
**Stoma creation**		**√**		
**Surgical complications**		**√**		
**Surgical drain placement**		**√**		
**Surgery report**		**√**		
**Time of drain removal**			**√**	
**Length of stay in hospital**			**√**	
**Post-surgical complications**			**√**	**√**
**Abdominal wall ultrasound**				**√**
**Adverse events**	**√ continuously**			

^a^This includes use of any blood transfusions that should be inserted in the CRF as type (red blood cells. FFP, platelets)

• Visit 1: Screening and baseline visit: screening of patient, baseline examination, pre-surgery assessment, informed consent

• Visit 2: Treatment visit: surgery

• Visit 3: Discharge from hospital: recording of post-surgical complications

• Visits 4, 5, and 6: Post surgery follow-up visits: at 3, 6, and 12 months post-surgery. All patients will perform an abdominal wall ultrasound to document the presence or not of incisional hernia. At the last visit, the data collected is the same of the other visits. The patients are called 15 days prior to the follow-up visit to remind them of the appointment.

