### Sample size

No previous data exist on the efficacy of swine dermal collagen prosthesis in preventing incisional hernia in peritonitis patients. The following published data will be used in our sample size calculation:
“The risk of incisional hernia in patients with peritonitis is elevated, with an incidence of up to 54%, compared with an incidence of 11–26% in general surgical population” [1–3, 20].“The result of this pooled analysis suggests a benefit to prophylactic mesh placement during laparotomy closure in high-risk patients with a significantly reduced incidence of incisional hernia without any significant differences in seroma formation and wound infection rate” [19].“The use of biologic mesh for ventral hernia repair results in less infectious wound complications but similar recurrence rate compared with non-biologic mesh” [18].

The sample size has been calculated using statpages.org (proportion difference power/sample size calculation). The sample size was defined in 90 patients (45 in each arm).

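### The question is set for contaminated or infected fields, but eligibility rests on pre-operative signs and suspicion, and the fate of randomised patients whose field proves clean is left undefined

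*Protocol article*

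**What the plan says.** - **Objective.** The primary aim is to "reduce the incisional hernia rate (from 50% to 20%) in patients undergoing urgent/emergent laparotomy in contaminated/infected field with peritonitis". Patients recruitment and the Discussion use the same framing.
- **Inclusion (Eligibility criteria).** Besides age and an indication for midline laparotomy, the patient needs clinical, laboratory or radiological evidence of peritonitis, joined by and/or. The list includes "fever, free air/fluid in abdominal cavity, leukocytosis, increased PCR, lactic dehydrogenase (LDH), tachycardia, tachypnea, clinical or radiological evidence/suspect of bowel ischemia". A further criterion concerns suspected bacterial translocation, with bowel overdistension and intestinal occlusion among its examples. All criteria must be met.
- **Exclusion and withdrawal (Informed consent subsection).** On peritonitis, the exclusion removes only patients with no evidence of it at all. Patients judged unsuitable during surgery are withdrawn; the article does not define unsuitable.
- **Randomisation (Patients recruitment).** It takes place before the laparotomy, when the surgeon enters the patient in the online form. "The randomization is simple and the allocation is 1:1 to each arm".
- **Field data (Visit procedures, Table 1).** Contamination assessment, peritonitis grade and "Peritoneal fluid sampling for microbiological examination" are all Visit 2 items, recorded at surgery. Nothing ties them to eligibility or to the withdrawal rule.

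**The concern.** The population in the question is not the population the criteria define. At randomisation the state of the field is presumed; it becomes known only once the abdomen is open. Some randomised patients may then prove to have a clean field, and the plan does not say what happens to them.

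There are two possible routes, and each has a cost:

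- **They stay.** The trial then estimates the effect in suspected peritonitis but words its conclusion for contaminated or infected fields. If their hernia risk is lower than 50%, the absolute difference shrinks.
- **They are withdrawn as unsuitable.** The exclusion then follows randomisation, has no stated criterion, and is made by a surgeon who can know the allocation. It could differ by arm. In the mesh arm a clean field may prompt the question whether to implant, whereas in the control arm standard closure goes ahead either way. The groups analysed would then no longer be the groups randomised.

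**Working it through.** **1. The plan's own figure.** Inputs: 50% v 20% (Objective); "All statistical comparisons will be based on two sided tests with a 5% significance level" (Statistical analysis); 1:1 allocation; "The sample size was defined in 90 patients (45 in each arm") (Sample size). The article states no power, so 80% is assumed.

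With mean rate 0.35 and difference 0.30:

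n = [1.96·√(2·0.35·0.65) + 0.842·√(0.5·0.5 + 0.2·0.8)]² / 0.30² = 38.5 per arm.

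Continuity correction: n′ = (n/4)·[1 + √(1 + 4/(n·0.30))]² = 44.9, so 45 per arm and 90 in total. The stated size is reproduced, with nothing left over for clean-field patients. Exact power of the uncorrected chi-square test at 45 v 45 is 0.868.

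**2. If clean-field patients stay.** Let f be their share, an assumption because the documents give none. For their control risk the nearest figures are in Background and rationale: "The incidence of IH in patients operated with peritonitis is up to 54%, compared with an incidence of 11–26% in the general surgical population". The 11% to 26% describes general surgery, not emergency laparotomy, so 40% is added as a further assumed value.

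The target odds ratio is (0.2/0.8)/(0.5/0.5) = 0.25. Applied to clean-field patients, it gives mesh risks of 3.0%, 8.1% and 14.3% for control risks of 11%, 26% and 40%.

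Mixed rate in each arm = (1 − f)·(50% or 20%) + f·(clean-field rate).

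At f = 20%:

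| Clean-field control risk | Control | Mesh | Difference (points) | Exact power, 45 v 45 |
|---|---|---|---|---|
| 11% | 42.2% | 16.6% | 25.6 | 0.785 |
| 26% | 45.2% | 17.6% | 27.6 | 0.830 |
| 40% | 48.0% | 18.9% | 29.1 | 0.857 |

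For 11% to 26% control risk, power is 0.830 to 0.850 at f = 10% and 0.737 to 0.808 at f = 30%.

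A harsher assumption is no mesh effect in clean fields. At f = 20% the rates are then 42.2% v 18.2% or 45.2% v 21.2%, and normal-approximation power is 0.71 or 0.68, against 0.86 undiluted by the same formula.

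**3. If clean-field patients are withdrawn and not replaced.** The contrast stays at 50% v 20%, but at f = 20% only 45 × 0.8 = 36 per arm remain and exact power is 0.787. At f = 30% about 32 per arm remain (45 × 0.7 = 31.5) and it is 0.734. These figures assume withdrawal unrelated to arm. Any bias from arm-related withdrawal comes on top and cannot be sized from the documents.

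**The case against.** Several counter-arguments have force.

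- **Entry is not on a single sign.** A reader might infer that one non-specific sign is enough. The criteria also list suspected translocation, and all must be met. This stands. However, that criterion is itself a pre-operative suspicion, and its wording leaves unclear whether it is compulsory. It does not require a contaminated field either.
- **Obstruction is an intended case.** Occlusion and overdistension are named as translocation risks, so such patients are not slipping through. This stands. Enrolling on suspicion is a defensible choice when the field is known only at surgery; the mismatch is with the wording of the objective and conclusion.
- **Dilution is not certain.** A reader might infer that clean-field patients do enter the analysis and dilute it. The documents do not support that: recruitment is described as being for contaminated or infected fields, and the surgical withdrawal rule may remove these patients. But the rule is undefined, so removal exchanges dilution for possible selective exclusion.
- **The power loss may be small.** At 40% clean-field risk it is about one percentage point. This stands.
- **Subgroup analyses may be in an SAP that is not shown.** This stands. The article's silence on analysis by field status is not itself the defect.
- **Safety.** A reader might infer diluted infection harm from the mesh. The Introduction ties its infected-field safety concern to intraperitoneal non-absorbable mesh, whereas this trial places a biological prosthesis behind the muscle. That argument is therefore weak.

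**Conclusion.** The mismatch holds: no criterion requires the field on which the objective and target are framed, and the plan leaves open whether randomised patients with a clean field stay or go. The main harm is to interpretation, together with an avoidable route to biased exclusion.

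The effect on power is illustrative only. Exact power is 0.87 with no clean-field patients and about 0.79 to 0.86 at an assumed 20% share, taking 11% to 40% control risk and a common odds ratio of 0.25. The share, the risks and the common effect are all assumptions.

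It might seem to follow that the trial's conclusion should rest on patients with a confirmed contaminated field. That is not supported. This set is defined after randomisation, partly by surgeons who can know the arm, and its exact power at 36 per arm (0.787) is no better than that of the diluted full set (0.785 to 0.830 for 11% to 26% risk).

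**What to change.** 1. State that findings at surgery do not remove a randomised patient from follow-up or from the primary comparison.
2. Describe the primary population, and word the primary conclusion, as patients with suspected peritonitis at randomisation. The sponsor should reconcile the eligibility wording with the objective on this point.
3. Pre-specify, as a supportive analysis, the hernia and wound-infection comparisons by field status, with the arm-by-field contrast and confidence intervals. Define field status before any look at outcomes, from the Visit 2 items scheduled for both arms: contamination assessment, peritonitis grade and peritoneal fluid microbiology.

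The cost is protocol and SAP wording plus one analysis on data already scheduled for collection. The article reports six patients enlisted, so the change comes early. The price is that the confirmed-field estimate is less precise (about 36 per arm at 20% clean) and can only support the primary result, not replace it.
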